## Abstract

**Background:**

Basic management for patients who have suffered a cardiac arrest and are admitted to an intensive care unit (ICU) after resuscitation includes setting targets for blood pressure and managing sedation and temperature. However, optimal targets and management are unknown.

**Methods:**

The STEPCARE (Sedation, Temperature and Pressure after Cardiac Arrest and Resuscitation) trial is a multicenter, parallel‐group, randomized, factorial, superiority trial in which sedation, temperature, and blood pressure strategies will be studied in three separate comparisons (SED‐CARE, TEMP‐CARE, and MAP‐CARE). The trial population will be adults admitted to intensive care who are comatose after resuscitation from out‐of‐hospital cardiac arrest. The primary outcome will be all‐cause mortality, and the secondary outcomes will be poor functional outcome (modified Rankin Scale 4–6), Health‐Related Quality of Life using EQ‐VAS, and specific serious adverse events in the intensive care unit predefined for each trial. All outcomes will be assessed at 6 months after randomization. The prognosticators, outcome assessors, statisticians, data managers, steering group, and manuscript writers will be blinded to treatment allocation. This statistical analysis plan includes a comprehensive description of the statistical analyses, handling of missing data, and assessments of underlying statistical assumptions. Analyses will be conducted according to the intention‐to‐treat principle, that is, all randomized participants with available data will be included. The analyses will be performed independently by two statisticians following the present plan.

**Conclusion:**

This statistical analysis plan describes the statistical analyses for the STEPCARE trial in detail. The aim of this predefined statistical analysis plan is to minimize the risk of analysis bias.

## BACKGROUND

1

Critical care management for patients who have suffered an out‐of‐hospital cardiac arrest (OHCA) who require treatment in an intensive care unit (ICU) includes setting goals and targets for the use of medications and devices that influence vital signs and other physiological parameters for the purpose of reducing ischemia–reperfusion injury. Sedation, temperature management, and blood pressure strategies are common examples of how clinicians deploy therapies in this patient population; however, optimal targets are unknown.^1^, ^2^

The STEPCARE trial is a multicenter, parallel‐group, non‐commercial, randomized, factorial, superiority trial in which sedation, temperature, and blood pressure strategies will be studied. The STEPCARE trial is a continuation of the collaborations from the previous Target Temperature Management after out‐of‐hospital cardiac arrest trial (TTM),^3^ Targeted Hypothermia versus Targeted Normothermia after Out‐of‐hospital Cardiac Arrest trial (TTM2),^4^ and the Carbon dioxide, Oxygen and Mean arterial pressure After Cardiac Arrest and Resuscitation trial (COMACARE).^5^

Through STEPCARE, this international collaboration aims to improve the evidence for critical care in cardiac arrest patients. Here we describe the statistical analysis plan that will outline the statistical analyses for the STEPCARE trial in detail.

## METHODS

2

The STEPCARE trial is registered at clinicaltrials.gov (NCT05564754, 2022‐10‐03). We describe the STEPCARE trial design and its intervention in detail in three separate protocols. In brief, the trial population will be adults (≥18 years) admitted after OHCA with the return of spontaneous circulation (ROSC). Patients will be eligible for enrolment if they meet all the following inclusion criteria and none of the exclusion criteria:

### Inclusion criteria

2.1

Out‐of‐hospital cardiac arrestA minimum of 20 min without chest compressions (20 min of spontaneous circulation without the need for chest compressions)Unconsciousness defined as not being able to obey verbal commands (Full Outline of UnResponsiveness (FOUR) score motor response of <4) or being intubated and sedated because of agitation after sustained ROSC.Eligible for intensive care without restrictions or limitationsInclusion within 4 h of ROSC

### Exclusion criteria

2.2

Trauma or hemorrhage (including gastrointestinal bleeding) as presumed cause of arrestOn Extracorporeal Membrane Oxygenation (ECMO) prior to randomizationPregnancySuspected or confirmed intracranial hemorrhagePreviously randomized in the STEPCARE trial

### Randomization and blinding

2.3

Trial sites will have access to an internet‐based application for immediate randomization to ensure adequate allocation concealment and sequence generation. Each patient will be assigned to three trials simultaneously. Randomization will be performed with permuted blocks of varying size, stratified for trial site only. Investigators will be blinded to the block sizes. The team treating the patient (physicians, nurses, and others) will not be blinded to the allocation group due to the inherent difficulty in blinding the interventions (sedation, temperature, and arterial pressure). Measures will be taken to ensure that the information about allocation will not be disseminated beyond the immediate group of caregivers responsible for patient care. The clinicians performing neuroprognostication, outcome assessors, statisticians, data managers, steering group, and manuscript writers will be blinded to treatment allocation.

### Trial interventions

2.4

The STEPCARE trial includes three separate comparisons.

### The SED‐CARE trial

2.5

In the SED‐CARE trial, participants are randomized to either continuous deep sedation or minimal sedation. Initially, patients could be sedated to ensure safe transport, imaging, coronary angiography, and other invasive procedures. Following randomization, the Richmond Agitation‐Sedation Scale (RASS) score and FOUR score motor response will be collected every 4 h. For patients randomized to continuous deep sedation, the target will be a RASS from −4 to −5 upon admission to the ICU and continued sedation until 36 h after randomization. In patients randomized to minimal sedation, sedative agents should be used only as needed for clinical care. After the 36‐h intervention period, the sedation strategy for both groups will be at the discretion of the treating physician as needed for clinical care.

### The TEMP‐CARE trial

2.6

In the TEMP‐CARE trial, participants are randomized to fever management with or without a device. The intervention period will commence immediately after randomization. Core body temperature will be continuously monitored (preferentially via a bladder catheter, but an alternative core temperature site such as esophagus or blood will be allowed). For participants allocated to fever management with a device, temperature management devices will be started to achieve a core body temperature of ≤37.5°C if the temperature reaches the trigger of ≥37.8°C within 72 h of randomization. For participants allocated to fever management without a device, fever will be managed as per standard treatment for any critically ill patient in the ICU, including exposure and pharmacological agents, where considered clinically necessary. The temperature intervention will last until 72 h after randomization, or until extubation, whichever occurs first. If the participant regains consciousness and does not require invasive ventilation prior to 72 h after randomization, then temperature management is at the discretion of the treating clinician. After discharge from the intensive care unit, temperature management is also at the discretion of the treating clinician.

### The MAP‐CARE trial

2.7

In the MAP‐CARE trial, participants are randomized to a mean arterial pressure (MAP) target of either >85 mmHg or >65 mmHg. All patients must have invasive monitoring of blood pressure. The intervention period will commence immediately after randomization, but titration of vasopressors to the MAP target may be delayed until the patient has completed the required diagnostic work‐up (e.g., computed tomography scan or coronary angiography) and is admitted to intensive care. The means to achieve the desired MAP target will be up to the treating clinician, but the primary recommendation is to titrate a vasopressor unless the patient is hypovolemic, in which case judicious doses of fluids should be prescribed. The MAP intervention will last until 72 h after randomization, or until extubation, whichever occurs first. After 72 h, or earlier if the participant regains consciousness and is extubated, and after discharge from intensive care, the management of MAP will be at the discretion of the treating physician.

### Outcomes

2.8

The primary assessment time point will be 6 months after randomization for all outcomes. The outcomes are defined as primary, secondary, and exploratory. The sample size is based on the primary outcome, and our primary conclusions will be based on the results of the primary outcome.

Primary outcomeAll‐cause mortality

Secondary outcomesProportion of participants with a poor functional outcome measured at 6 months after randomization in either one of two ways (hierarchical order):Using the modified Rankin Scale (mRS) with mRS 4–6 indicating a poor outcome (dichotomized)OR if a mRS score cannot be assigned using the standardized assessment, a poor outcome (yes/no) will be based on whether the patient is dependent on others for basic activities of daily living (moving indoors, eating, dressing, personal hygiene)
Proportion of patients with a predefined serious adverse event in the index intensive care stay (defined differently for each trial):In *SED‐CARE*: death, sepsis or septic shock (Sepsis‐3 criteria),^6^ arrhythmia requiring defibrillation, cardioversion or chest compressions, venous thromboembolism, reintubation, or unplanned extubationIn *TEMP‐CARE*: death, sepsis or septic shock (Sepsis‐3 criteria),^6^ arrhythmia requiring defibrillation, cardioversion or chest compressions, venous thromboembolism, moderate or severe bleeding (GUSTO criteria)^7^
In *MAP‐CARE*: death, arrhythmia requiring defibrillation, cardioversion, or chest compressions, moderate or severe bleeding (GUSTO criteria),^7^ acute kidney injury with renal replacement therapy, limb ischemia requiring radiological or surgical intervention, or gut ischemia demonstrated at laparotomy/laparoscopy or clinically suspected based on abdominal CT‐scan
Patient‐reported Health‐Related Quality of Life (HRQoL) using EQ‐5D‐5L measured by EQ‐VAS.^8^

### Exploratory outcomes

2.9

mRS (ordinal score)Ventilator‐free days within 30 daysHospital/institution‐free days alive within the first 30 days

### Sample size and power estimations

2.10

Based on the results of the TTM trial, TTM2 trial, and information from the International Cardiac Arrest Registry (INTCAR),^9^ we estimate that within 6 months after randomization, approximately 60% of the participants will die. We hypothesize that 6 months after randomization, 54.4% of the participants will die in the intervention groups, corresponding to a relative risk reduction of 9% (relative risk, RR = 0.91). With an acceptable risk of type‐1 error of 5% and an acceptable risk of type‐2 error of 10% (power of 90%), a total of 3278 participants (1639 in each pairwise comparison) would be required.

We plan to investigate the possible effects of adjustment for site and possible interactions between interventions using simulations.^10^ Preliminary simulations suggest that if there are interactions between the trial interventions on outcomes, it would be necessary to increase the sample size. The STEPCARE trial is being conducted with the assumption that there will be no such interactions between the trial interventions on outcomes. However, to accommodate the possibility of minor interactions, an increase in the sample size (5%) has been chosen to account for this. The combined effect of withdrawn consent and missing data on the primary outcome in the TTM2 trial resulted in a sample size reduction of approximately 2%. We assume a similar result in the current trial (1.8%). Considering the above‐mentioned factors, we will increase the sample size by 6.8% and recruit a total of 3500 participants.

We estimated the statistical power of all secondary outcomes.^11^ With an estimated sample size of 3500 participants in total, the functional outcome measure (dichotomized mRS) has a power of 98% to detect a relative risk of 0.90 for a poor functional outcome (mRS 4–6) in the experimental group, with 65% of cases in the control group experiencing a poor functional outcome.

For the predefined serious adverse events, we performed simulations to assess the incidences for the three serious adverse event outcomes. We had estimated incidences for arrhythmia, sepsis, and bleeding, but not for unplanned extubation, reintubation, and venous thromboembolism.^12^, ^13^ We also considered aggregate data from previous meta‐analyses and trials, and these numbers roughly corresponded to the simulations:^3^, ^4^, ^14^, ^15^, ^16^
In SED‐CARE: We estimate a power of 92% to detect a relative risk reduction or increase of 9% for the predefined serious adverse events with 61% of cases in the control group.In TEMP‐CARE: We estimate a power of 92% to detect a relative risk reduction or increase of 9% for the predefined serious adverse events with 63% of cases in the control group.In MAP‐CARE: We estimate a power of 91% to detect a relative risk reduction or increase of 10% for the predefined serious adverse events with 57% of cases in the control group.The anticipated intervention effects in the above‐mentioned sample size and the power estimations correspond to an absolute risk reduction of 5.6%.

We estimate a power of >90% to detect a difference in 5 points on the EQ‐5D‐5L VAS scale, based on a mean value of 75 in the control group and a standard deviation of 20 points.^4^

### General analysis principles

2.11

We will conduct all analyses according to the intention‐to‐treat principle (ITT), that is, all randomized participants with available data will be included in all analyses.

We will assess if the statistical and clinical significance thresholds are crossed (Bayes factor calculations will be reported in supplementary material).^17^ Assessment of clinical significance will be based on the anticipated intervention effects used in the sample size and power estimations.^17^ Our primary conclusion will be based on the primary outcome, so all tests of statistical significance (including subgroup analyses) will be two‐sided with a threshold of 5%.^17^ No conclusions will be drawn based on secondary outcomes.

It is generally acknowledged that regression analyses ought to be adjusted for the stratification variables used in the randomization.^18^, ^19^, ^20^ Hence, when analyzing each of the three trials, we will adjust all analyses for ‘site’ and the allocated intervention in the two other trials (e.g., the SED‐CARE outcomes will be adjusted for ‘site’ and the allocated TEMP‐CARE and MAP‐CARE interventions). We will assess whether there are significant interactions between trial interventions (for details, see Section 2.14).

We will perform the following subgroup analyses:Age (higher or lower than the median)Sex (male/female)Cardiopulmonary resuscitation by bystander (yes/no)Initial rhythm (shockable vs. non‐shockable)Time to ROSC (higher or lower than the median)Circulatory status on admission (presence or absence of circulatory shock diagnosed by the treating physician)Baseline risk of poor neurologic outcome (Miracle2‐score: low risk (0–2), medium (3–5), and high (6–10).^21^)Presumed cause of arrest at randomization (cardiac vs. others)Chronic hypertension as a comorbidity

We plan to reanalyze all three trials using Bayesian statistics. Separate statistical analysis plans will be published.

### Statistical analyses

2.12

#### Outcomes

2.12.1

We will analyze the primary outcome as a binary variable (alive or dead). We will analyze the secondary outcomes as follows: (I) We will evaluate the functional outcome by dichotomizing the modified Rankin scale (0–3 vs. 4–6), or if this is missing, dependent versus independent in basic activities of daily life (moving indoors, eating, dressing, personal hygiene). (II) We will analyze serious adverse events as a binary variable (one or more versus no serious adverse event). Additionally, we will present each specific serious adverse event separately by risk ratios and 95% confidence intervals. (III) We will analyze HRQoL by EQ‐VAS scale as a continuous variable (0–100).

#### Analysis of dichotomous data

2.12.2

We will present dichotomized outcomes as proportions of participants in each group with the event, as well as relative risks with 95% confidence intervals. We will analyze dichotomous outcomes using mixed effects generalized linear models using a log‐link function with ‘site’ as a random intercept using an exchangeable covariance matrix, and we will include the allocated intervention in the two other trials as fixed effects. If the analysis does not converge, we will use mixed effects logistic regression to analyze dichotomized data and relative risks will be obtained using either G computation in R (R Core Team, Vienna, Austria) or the NLCOM command in Stata 18 (StataCorp, College Station, TX, USA).

#### Analysis of continuous data

2.12.3

We will present continuous outcomes as means and standard deviations for each group, along with 95% confidence intervals for the means of the groups and the mean differences between the groups. We will analyze continuous outcomes using mixed effects linear regression with ‘site’ as a random intercept using an exchangeable covariance matrix, and we will include the allocated intervention in the two other trials as fixed effects. We expect that a large proportion of the participants will die before the assessment of HRQoL. When assessing health‐related HRQoL, we will, therefore, in a secondary analysis, impute a ‘0’ for all participants who died. We will analyze these data using the stratified Wilcoxon test stratified for the other interventions.

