### Handling of missing data

2.13

In the primary analysis we will include all randomized participants with available data (please see the Section 2.12.3). We will handle missing data according to the recommendation by Jakobsen et al.^22^ In short, we anticipate that the proportion of missing values on main dichotomous outcomes will be less than 5%. We will consider using multiple imputations and present best‐worst and worst‐best case scenarios if it is not valid to ignore missing data.^22^ Best‐worst and worst‐best case scenarios assess the potential range of impact of the missing data for the trial results.^22^ In the best‐worst case scenario, it is assumed that all patients lost to follow‐up in the experimental group had a beneficial outcome (survived, had no poor functional outcome, etc.), and all those with missing outcomes in the control group had a harmful outcome (did not survive, had poor functional outcome, etc.).^22^ Conversely, in the worst‐best case scenario, it is assumed that all patients who were lost to follow‐up in the experimental group had a harmful outcome and that all those lost to follow‐up in the control group had a beneficial outcome.^22^ When continuous outcomes are used, we will define a beneficial outcome as the group mean plus two SDs of the group mean (fixed imputation), and a harmful outcome as the group mean minus two SDs of the group mean (fixed imputation).^22^

We will perform sensitivity analyses assuming that all participants with missing data were either all alive or dead.

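### Both EQ-VAS analyses give a value only to the dead, so survivors without a self-report drop out although their 6-month functional status is assessed

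*SAP article*

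**What the plan says.** Section 2.8 of the SAP article lists the outcome as "Patient‐reported Health‐Related Quality of Life (HRQoL", with EQ-VAS as the measure. On timing: "The primary assessment time point will be 6 months after randomization for all outcomes".

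Section 2.11 sets the analysis population: "all randomized participants with available data will be included in all analyses".

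Section 2.12.3 then gives two EQ-VAS analyses:
- Main analysis: "We will analyze continuous outcomes using mixed effects linear regression", with site as a random intercept and the other two allocations as fixed effects. No value is assigned to anyone without a measurement.
- Secondary analysis: a zero is imputed "for all participants who died. We will analyze these data using the stratified Wilcoxon test stratified for the other interventions". No other group receives a value.

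Section 2.13 repeats the available-data rule and refers back to 2.12.3. If ignoring missing data is judged not valid, multiple imputation will be considered and best-worst and worst-best scenarios presented. For continuous outcomes the scenarios use the group mean plus or minus two SDs. On the expected amount, the section says "we anticipate that the proportion of missing values on main dichotomous outcomes will be less than 5" per cent. It states no expectation for EQ-VAS.

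The functional outcome is treated differently. Where an mRS score cannot be assigned, sections 2.8 and 2.12.1 substitute dependence in basic activities of daily living.

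**The concern.** After cardiac arrest, a missing self-report in a survivor is plausibly related to brain injury, and so to the quantity being measured. Such a survivor has no available value for the regression and is not among the dead for the Wilcoxon test, so both analyses lose the same people. The deaths-as-zero analysis is there because many participants die before assessment, yet it does not cover all randomized participants either.

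If the share of non-reporting survivors differs between arms, each comparison is partly one of who could answer. The regression can miss a difference among survivors. The rank test can shift either way, because removing survivors from an arm raises the proportion of deaths among those left in it.

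The plan anticipates the parallel difficulty for mRS and provides a fallback. That same 6-month assessment says something about the missing EQ-VAS values, but the plan does not use it for them.

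**Working it through.** **The plan's own figure.** Section 2.10 claims more than 90% power for 5 points with SD 20. On expected survivors only, the arms have 1750 × 0.400 = 700 and 1750 × 0.456 = 798. The standard error is 20 × √(1/700 + 1/798) = 1.036, so z = 5/1.036 − 1.96 = 2.87 and power is 99.8%. The claim is reproduced. With half of the survivors missing, power is still 92.7%. The issue is bias, not power.

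**Size of the group at risk.** Inputs from section 2.10: mortality 60% versus 54.4%; control poor outcome ("with 65% of cases in the control group experiencing a poor functional outcome"); relative risk 0.90 for poor outcome; 3500 participants, so 1750 per arm.
- Control mRS 4-5: 65 − 60 = 5% of randomized, about 88 participants. Share of survivors: 5/40 = 12.5%.
- Intervention poor outcome: 0.90 × 65 = 58.5%. mRS 4-5: 58.5 − 54.4 = 4.1% of randomized, about 72 participants. Share of survivors: 4.1/45.6 = 9.0%.

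**Assumptions, not in the document.** EQ-VAS is 40 in mRS 4-5 and 80 in mRS 0-3. These values reproduce the planned control mean: (0.05 × 40 + 0.35 × 80)/0.40 = 75. No mRS 4-5 survivor reports, which is the upper end within that group.

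The rank effect is P(intervention better) + ½P(tie) − 0.5, with order dead < mRS 4-5 < mRS 0-3 and ties within each class. Control proportions are (0.60, 0.05, 0.35).

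*Scenario A, the plan's hypothesized effects: intervention (0.544, 0.041, 0.415).*
- Intervention survivor mean: (0.041 × 40 + 0.415 × 80)/0.456 = 76.4. True difference +1.4; among reporters 80 − 80 = 0.
- Rank effect, everyone kept: 0.041 × 0.60 + 0.415 × 0.65 + ½(0.544 × 0.60 + 0.041 × 0.05 + 0.415 × 0.35) − 0.5 = 0.0312.
- Rank effect, mRS 4-5 dropped: ½(0.415/0.959 − 0.35/0.95) = 0.0322.

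*Scenario B, all averted deaths become mRS 4-5: intervention (0.544, 0.106, 0.35).*
- Intervention survivor mean: (0.106 × 40 + 0.35 × 80)/0.456 = 70.7. True difference −4.3; among reporters 0. If half of the mRS 4-5 survivors report, it is 74.7 − 77.3 = −2.6.
- Rank effect, everyone kept: 0.106 × 0.60 + 0.35 × 0.65 + ½(0.544 × 0.60 + 0.106 × 0.05 + 0.35 × 0.35) − 0.5 = 0.0182.
- Rank effect, mRS 4-5 dropped: ½(0.35/0.894 − 0.35/0.95) = 0.0115. If half report, 0.0152.

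**Simulation check** (1000 runs, 1750 per arm, 60% mortality in both arms, reporters with mean 75 and SD 20, non-reporters with true mean 30 and SD 10, unstratified tests). With 12.5% non-reporting in each arm, every analysis rejected in 4-5% of runs. With 20% versus 5%, the reporters-only t-test rejected in 4.8%. The deaths-as-zero Wilcoxon test rejected in 62% with non-reporters dropped and 26% with their values kept. The excess arises because dropping survivors makes deaths 0.60/(0.60 + 0.40 × 0.80) = 65.2% of one arm and 0.60/(0.60 + 0.40 × 0.95) = 61.2% of the other.

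**What section 2.13 would supply.** At mean 75 and SD 20, the scenario values are 75 + 40 = 115 and 75 − 40 = 35. The first lies outside the 0-100 scale that section 2.12.1 states for EQ-VAS. In each scenario one arm's non-reporters all receive the favourable value, whatever their functional status.

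**The case against.** The case against has real force.

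- **Section 2.13 is not empty.** A reader might infer that optional imputation is the only cover, or that it is triggered by the 5% expectation. The document supports neither. The best-worst scenarios extend explicitly to continuous outcomes, and their harmful value of 35 is below the 40 assumed above. The trigger is whether ignoring missing data is valid, stated separately from the 5% figure. What remains is that the cover depends on a later judgement, names no imputation model and does not use functional status.
- **Inability to report is inferred.** The document says patient-reported and no more. A proxy or assistance rule may stand in the protocol, which is not shown, and no non-response figure is given.
- **Scenario B is not the plan's hypothesis.** A reader might take its loss of (0.0182 − 0.0115)/0.0182 = 37% in rank effect as the expected consequence. It requires mRS 4-5 to rise from 5% to 10.6%, whereas the plan's figures imply a fall to 4.1%. Under those figures the rank effect changes by about 3%, upwards. The −4.3 points also reflect extra survivors entering the average, not a decline in any patient's quality of life.
- **Severe disability is visible elsewhere.** The dichotomized mRS with its fallback and the ordinal mRS do not need a self-report. It would be wrong to infer that the plan cannot detect survival with severe disability.
- **The stakes are limited.** Section 2.11 draws no conclusions from secondary outcomes.

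These points limit the size and certainty of the bias. They do not alter the fact that both specified EQ-VAS analyses drop living non-reporters.

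**Conclusion.** The point holds as a gap in the specification of a secondary outcome. Survivors without a self-reported EQ-VAS are in neither analysis in section 2.12.3, and the conditional tools in 2.13 do not use the functional result assessed at the same 6-month time point.

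Bias arises if non-reporting differs by arm, and neither its size nor its direction is fixed. If no mRS 4-5 survivor reports and EQ-VAS is 40 and 80 in the two groups, the unseen survivor difference is +1.4 points at the plan's hypothesized effects. It is −4.3 points if averted deaths all become mRS 4-5, against a 5-point target. The rank effect moves from 0.031 to 0.032 in the first case and from 0.018 to 0.012 in the second. The extent of non-reporting and the EQ-VAS values are assumptions. The 12.5% and 9.0% shares follow from the plan's rates.

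The mortality conclusion is unaffected. The change is worth making because it is cheap and uses a 6-month assessment already planned.

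**What to change.** In sections 2.12.3 and 2.13:
- Make multiple imputation the stated method for missing EQ-VAS in survivors, with 6-month mRS (or dependence in activities of daily living where mRS is missing) in the imputation model.
- Add a sensitivity version of the deaths-as-zero Wilcoxon test in which survivors recorded as unable to self-report are ranked just above death.
- Show the complete-case result beside both.
- Report by arm the number of survivors without an EQ-VAS value.
- If the protocol has a proxy rule, refer to it here.

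The cost is SAP wording and a reason-for-missing code at the existing 6-month contact. There are two drawbacks. The placement just above death is a convention, which is why it belongs in a sensitivity analysis. And if few mRS 4-5 survivors report, the imputation extrapolates from little information; the count by arm lets readers judge that.
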